#### Perioperative management, discharge, and follow-up

After being discharged from the hospital, patients will be followed up at the surgical clinic for PRO collection, which can be done in person or virtually. Other clinical outcomes such as nutritional assessment, disease recurrence, and survival will be collected retrospectively through medical records.

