## Methods/design

This is a multicenter, open-label, prospective cohort study comparing outcomes of MIPG (trial procedure) and MITG (standard of care, control group). We expect to enroll a total of 60 patients in this study (30 per group). Patients will be recruited from and treated at MD Anderson Cancer Center, Mayo Clinic, Memorial Sloan Kettering Cancer Center, Yonsei University, and Keio University, after Institutional Review Board approval for each institution. We plan to enroll at least 20 patients each from Asian (Keio University and Yonsei University) and US (MD Anderson, and Mayo Clinic Minnesota, and Memorial Sloan Kettering Cancer Center) institutions. The total study duration is expected to be 60 months (including enrollment and follow-up). We will prospectively collect PROs longitudinally for a 1-year period. Other clinical factors will also be collected to investigate factors associated with improved PROs.

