#### Posttreatment outpatient evaluation

Post-discharge follow-up evaluations for PRO collection will occur at 1 month (± 2 weeks) and 3, 6, and 12 months (± 1 month) after surgery. These may be performed in person or by telephone, email, or website-based reporting system (REDCap), and data will be subsequently stored in the REDCap database, which will be managed at MD Anderson (center institution of this study).

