### Outcome measures

The primary endpoint is appetite level (reported on a 0–10 scale, in Q8 of MDASI-GI +) at 3 months after surgery. The individual and total MDASI-GI + scores will also be reported at baseline (preoperative) and 1, 3, 6, and 12 months after surgery.

The secondary endpoints below will be collected retrospectively from the medical record.

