#### Safety measures

The rate and types of postoperative complications within 90 days after surgery, length of post-operative hospital stay, and rate of post-discharge re-admission within 90 days after surgery will be recorded.

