#### Oncologic measures

The incidence of loco-regional recurrence and death within 3 years after MITG or MIPG will be recorded.

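### Ninety-day re-admission and 3-year recurrence and death are taken from the medical record alone, so events outside the study hospital may be missed

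*Protocol article*

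**What the plan says.** The source of the data is stated twice. Under Perioperative management, discharge, and follow-up: "Other clinical outcomes such as nutritional assessment, disease recurrence, and survival will be collected retrospectively through medical records". Under Outcome measures, as the lead-in to the nutritional, safety and oncologic measures: "The secondary endpoints below will be collected retrospectively from the medical record". The section Additional clinical data then lists re-admission, recurrence, date of last follow-up and vital status among items to be taken from the record where it holds them.

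The windows are longer than 30 days in one case and years long in the other. The long one stands under Oncologic measures: "The incidence of loco-regional recurrence and death within 3 years after MITG or MIPG will be recorded". The short one, for hospital returns, stands under Safety measures: "rate of post-discharge re-admission within 90 days after surgery will be recorded".

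The contacts with patients serve another purpose. Perioperative management, discharge, and follow-up: "patients will be followed up at the surgical clinic for PRO collection, which can be done in person or virtually". Posttreatment outpatient evaluation gives the timing: "Post-discharge follow-up evaluations for PRO collection will occur at 1 month (± 2 weeks) and 3, 6, and 12 months (± 1 month) after surgery". These contacts may be made in person, by telephone, by email or through REDCap. Methods/design sets the limit: "We will prospectively collect PROs longitudinally for a 1-year period".

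Statistical methods plans Kaplan-Meier estimates and Cox regression for loco-regional recurrence-free and overall survival, with surgical procedure as a factor, and a 3-year loco-regional recurrence rate with a 95% confidence interval.

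**The concern.** A chart holds what happened at that hospital and what was reported back to it. A patient who is re-admitted, relapses or dies elsewhere may leave no event there. For recurrence and survival there is a second problem. If deaths tend to be reported back while well patients simply stop attending, the survivors are censored early and the deaths are counted. If deaths elsewhere go unreported, the opposite happens. Kaplan-Meier and Cox methods need censoring that is unrelated to outcome, and taking items only where the record holds them does not secure this.

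The stake is the safety side of the study. The Background names incomplete node removal, with possible recurrence, as a theoretical disadvantage of proximal gastrectomy, and the abstract expects the study to establish benefit and safety. With about 60 patients, a few missed events are visible in the estimates.

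**Working it through.** The article states no expected figure for re-admission, recurrence or death, so there is no planned figure to reproduce on this point. The inputs are the contact schedule and the two windows. Months are converted at 30.44 days.

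**Contact windows, in days after surgery**

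| Contact | Earliest | Latest |
|---|---|---|
| 1 month ± 2 weeks | 16 | 44 |
| 3 months ± 1 month | 61 | 122 |
| 6 months ± 1 month | 152 | 213 |
| 12 months ± 1 month | 335 | 396 |

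**90-day window.** The 3-month contact may come 90 − 61 = 29 days before the window closes. The 6-month contact always follows it, by 152 − 90 = 62 to 213 − 90 = 123 days, and the 12-month contact by at least 335 − 90 = 245 days. So a contact after day 90 is scheduled for every patient. What the article does not describe is any question at these contacts about admissions to other hospitals.

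**3-year window.** The last contact falls at 11 to 13 months. The time left is 36 − 13 = 23 to 36 − 11 = 25 months, or 24/36 = 67% at the nominal date. No scheduled contact reaches month 36.

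**Share of events after the last contact.** Assume a constant hazard h and a 3-year risk r of 10% to 30%; neither is in the documents. Then h = −ln(1 − r)/36, and the share of 3-year events after month t is 1 − (1 − exp(−h·t))/r.

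| r | t = 11 | t = 12 | t = 13 |
|---|---|---|---|
| 10% | 68.3% | 65.5% | 62.7% |
| 20% | 67.0% | 64.2% | 61.3% |
| 30% | 65.6% | 62.6% | 59.7% |

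About 60% to 68% of the events would therefore fall after the last scheduled contact.

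**Illustration of the loss.** Assume 20% 3-year mortality, two thirds of deaths after month 12, and 10% to 30% of patients followed elsewhere with their deaths unseen. None of these is in the documents.

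- Deaths: 60 × 0.20 = 12
- After month 12: 12 × 2/3 = 8
- Unseen: 8 × 0.10 = 0.8 to 8 × 0.30 = 2.4
- As a share of 60 patients: 1.3 to 4.0 percentage points
- If all fell in one group of 30, the extreme case: 2.7 to 8.0 percentage points

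**The case against.** The strongest reply has four parts.

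First, a reader might infer that no patient contact is assured after the end of either window. For the 90-day window this is wrong: the 6- and 12-month contacts are scheduled for everyone and always fall after day 90. That objection stands in full. Only the narrower point remains, that these contacts are described for PROs and not for admissions.

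Second, the 1-year limit applies to PROs. The study is to last 60 months including follow-up, and date of last follow-up and vital status are on the data list. The article does not say that clinical care stops at 12 months, and the chart may contain reports from outside. This stands too: the gap is in scheduled study contact, and events may be missed; the documents do not show that they are.

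Third, a reader might infer that the bias runs by procedure, because sites may favour one operation and differ in how complete their charts are. The documents give neither the mix of procedures by site nor any measure of chart completeness. They say that procedure follows patient choice and surgeon discretion. A difference between groups is possible but not shown, and the direction of any bias is unclear.

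Fourth, an article condenses, and retrieval of outside records may be set out in the full protocol. That could soften the point. It does not remove it, because the record as the source, the purpose of the contacts and their end date are all stated choices. It is also fair that the loss is small beside sampling error: with 12 deaths in 60, the 95% Wilson interval is about 12% to 32%.

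**Conclusion.** The point holds for the 3-year outcomes, and in a narrower form for re-admission. Recurrence and death are read from the record alone, with no scheduled study contact for 23 to 25 of the 36 months, so events elsewhere may be missed or patients censored in a way related to outcome. For the 90-day outcomes, later contacts exist, but none is described as asking about treatment elsewhere, and the 3-month contact may precede day 90.

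The length of the gap follows from the documents. The loss of about 1 to 2 deaths (1.3 to 4.0 points) does not; it rests on the three assumptions above and is illustrative only. These are secondary endpoints. The primary endpoint, appetite at 3 months, and the sample size are untouched. The change is worth making because it is cheap, not because a large bias has been shown.

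**What to change.** 1. At the first already scheduled contact on or after day 90 (the 3-month contact if it is late enough, otherwise the 6-month contact), ask about re-admissions or complications treated at any hospital within 90 days of surgery.
2. Add a short remote check of recurrence and vital status at 24 and 36 months for all patients in both groups, through the telephone, email or REDCap channel already in use. Use the chart to confirm dates and details.
3. Censor at the date of last confirmed status, and report completeness of follow-up by group and by site, so that readers can see whether it differs.

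The cost is about two short remote contacts per patient, roughly 60 × 2 = 120 in all, one added question at an existing contact, and consent wording to cover contact to 36 months. No visit or procedure is added.

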#### Posttreatment outpatient evaluation

Post-discharge follow-up evaluations for PRO collection will occur at 1 month (± 2 weeks) and 3, 6, and 12 months (± 1 month) after surgery. These may be performed in person or by telephone, email, or website-based reporting system (REDCap), and data will be subsequently stored in the REDCap database, which will be managed at MD Anderson (center institution of this study).

### Outcome measures

The primary endpoint is appetite level (reported on a 0–10 scale, in Q8 of MDASI-GI +) at 3 months after surgery. The individual and total MDASI-GI + scores will also be reported at baseline (preoperative) and 1, 3, 6, and 12 months after surgery.

The secondary endpoints below will be collected retrospectively from the medical record.

#### Nutritional measures

Body weight and serum levels of albumin, ferritin, vitamin B_12_, hemoglobin, and ghrelin will be measured at baseline and 1, 3, 6, and 12 months after surgery.

#### Safety measures

The rate and types of postoperative complications within 90 days after surgery, length of post-operative hospital stay, and rate of post-discharge re-admission within 90 days after surgery will be recorded.

#### Oncologic measures

The incidence of loco-regional recurrence and death within 3 years after MITG or MIPG will be recorded.

#### Additional clinical data

The following data will be collected retrospectively if available in the medical record: treating institution (MD Anderson, Mayo Clinic, Memorial Sloan Kettering, Yonsei, or Keio), patient age, gender, race/ethnicity, body weight, height, use of concurrent medications such as opioids, initial diagnosis date, date of surgery, tumor size and location (diameter and esophageal extension above GEJ, Siewert classification, by endoscopic assessment), preoperative imaging (computed tomography, positron emission tomography, magnetic resonance imaging, endoscopic ultrasound) findings, type of preoperative therapy, laparoscopic findings, operating room time and blood loss, postoperative morbidity and mortality within 90 days after surgery, length of hospital stay, incidence of re-admission within 90 days after surgery, pathologic details (histologic type, TNM category, margin status), serum laboratory data (hemoglobin, leukocytes, absolute neutrophil count, platelet count, blood urea nitrogen, creatinine, albumin, pre-albumin, ghrelin, ferritin, vitamin B_12_) and date collected, recurrent disease (incidence, date, and location), and date of last follow-up and vital status.

The MDASI-GI is a validated questionnaire for measuring symptom severity and interference with function in patients with gastrointestinal cancers, including gastric cancer [19]. Using this questionnaire, patients score the severity of their symptoms over the previous 24 h on a scale of 0 (not present) to 10 (as bad as you can imagine). To further investigate patient symptom burden after gastrectomy, three additional questions, about the presence and degree of reflux, hot flashes, and dizziness, were added to the MDASI-GI to create the MDASI-GI + (Fig. 1). The rationale for adding these three questions is that acid and bilious reflux and dumping syndrome are two of the most common symptoms patients experience after major surgery for upper gastrointestinal cancers. Hot flashes and dizziness are frequently experienced with dumping syndrome.

### Translation of the MDASI-GI + into Korean, Japanese, and Spanish

The majority of the MDASI-GI questionnaire items were available in Spanish, Korean, and Japanese, but the three additional questions [items 25–27] had not been translated into the three languages and items 15–18 had not been translated into Japanese. We followed a standardized translation process as described below.Two translators who are fluent in both the requested language and English and who worked separately translated the text.One translator translated the written English items into the requested language in writing. This translation followed the established format, wording, and style of the rest of the MDASI translated into that language. The first translator was given a copy of the core MDASI in the requested language to facilitate this process.The second translator translated the written requested language items back into English in writing.The PI summarized the translation process and asked an experienced collaborator in the Symptom Management Department at MD Anderson to review and approve the written translations from English to the requested language and back to English. If the translations did not adequately convey the intended meaning of the items, we asked for new translations into the requested language and then back translations into English until a satisfactory translation was achieved.Approved translations were tested in 5 patients fluent in the translated language to confirm that the translated questions are easy to understand without creating confusion.

### Statistical methods

The primary outcome is appetite level score (with 0 being the best and 10 being the worst) according to the MDASI-GI + (Question #8) at 3 months after surgery. We will enroll a total of 64 patients in order to have 60 evaluable patients at 3 months after surgery (i.e., assuming a 5% attrition rate). With 30 patients expected in each cohort, this study will have 80% power to detect a one-point difference in appetite level score using a two-sample *t*-test with a 5% significance level and assuming a common standard deviation of 1.35 (nQuery Advisor 7.0). We will also compare serum ghrelin levels at 3 months after surgery. For the primary analyses, we will apply the inverse probability treatment weights using propensity scores for assessing the difference between the two surgical groups. Inverse probability weighting is applied by weighting the outcome measures by the inverse of the probability of an individual with a given set of covariates being assigned to their treatment (i.e., propensity score). The propensity scores will be derived through fitting a multiple logistic regression model with MIPG (vs. MITG) as the outcome variable. Then, in the presence of measured confounders, we can estimate the difference between the two treatment groups via inverse probability weighting of the study subjects. For the regression analyses described below for assessing the “surgical procedure” effect, the inverse probability treatment weights using propensity scores will be applied as appropriate in addition to any standard statistical methods. The two-sample t-test or Wilcoxon rank-sum test will also be used to compare the appetite level or ghrelin level at 3 months, as well as the percent change from baseline, between the two cohorts. We will longitudinally collect PROs (using the fully translated MDASI-GI +) and compare specific items and overall scores as well as body weight, body mass index, and albumin and hemoglobin levels at 1, 3, 6, and 12 months after surgery in the cohorts. A linear mixed effects model will be fit to assess the change in QoL over time while accounting for potential intra-patient correlations. “Time” points will be included as a fixed effect, and “patient” will be included as a random effect. The surgical procedure received and use of adjuvant or neoadjuvant therapy will be included as covariates. Similar analyses will be performed to assess the changes in body weight, body mass index, and albumin and hemoglobin levels over time. The number of LNs examined pathologically, incidence of postoperative complications, operating room time, blood loss, and length of hospital stay will be compared. Continuous variables (such as length of hospital stay) will be assessed using the two-sample t-test or Wilcoxon rank-sum test. Categorical variables (such as type and severity of complications) will be assessed using Fisher’s exact test. Local–regional recurrence-free and overall survival will be estimated using the Kaplan–Meier method, and Cox regression analyses will be performed to assess the association with patient characteristics and surgical procedure received. The 3-year loco-regional recurrence rate will be estimated along with the 95% confidence interval. Missing data will be excluded from analysis and no missing data imputation will be performed. Sensitivity analyses to investigate factors associated with PRO scores, including but not limited to country (west vs. east), tumor location, types of reconstruction after PG, use of neoadjuvant and adjuvant therapy, use of jejunostomy or nutrition status, on PRO scores will be performed.

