### Interventions

#### Preoperative evaluation

Within 30 days prior to surgery, PRO collection will be completed using the MDASI-GI + (Fig. 1). This can be done by paper or electronic-based communication (REDCap).

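### The stated primary analysis does not commit to using the pre-operative appetite score, in either the outcome model or the propensity model, although every patient is asked for it

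*Protocol article*

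**What the plan says.** - **Endpoint.** Outcome measures: "The primary endpoint is appetite level (reported on a 0–10 scale, in Q8 of MDASI-GI +) at 3 months after surgery". Statistical methods adds the direction of the scale, on which 0 is the best and 10 the worst score.
- **Baseline data.** Preoperative evaluation: "Within 30 days prior to surgery, PRO collection will be completed using the MDASI-GI" (the extended questionnaire). Outcome measures: "The individual and total MDASI-GI + scores will also be reported at baseline (preoperative) and 1, 3, 6, and 12 months after surgery". So the same item is available before surgery.
- **Primary analysis.** Statistical methods: "we will apply the inverse probability treatment weights using propensity scores for assessing the difference between the two surgical groups". The propensity score comes from a logistic model for procedure. Its covariates are described only in general terms and are not listed.
- **Other uses of baseline.** The same section adds a t-test or Wilcoxon test of the 3-month level and of percent change from baseline. The mixed model for change over time names procedure and (neo)adjuvant therapy as covariates, but not the baseline score.
- **Power.** "this study will have 80% power to detect a one-point difference in appetite level score". The calculation behind this is an unadjusted t-test of 3-month scores at the 5% level, with an SD of 1.35 assumed in both groups.
- **Allocation and missing data.** Details of surgery leaves the procedure to patient choice and surgeon discretion. Statistical methods excludes missing data and rules out imputation.

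**The concern.** In a preference-allocated study of 60 patients, appetite before surgery is an obvious candidate for a variable that differs between groups and also predicts appetite afterwards. The Discussion itself expects factors such as neoadjuvant therapy to affect patient-reported outcomes. The stated primary estimate compares 3-month scores, and nothing in the article secures the use of the pre-operative score in it.

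Two things are at stake. The first is precision: a covariate correlated with the outcome reduces residual variance. The second is confounding: if baseline appetite is related to the choice of procedure and is missing from the propensity model, part of that difference carries into the result.

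The percent-change comparison does not fill the gap. It is not primary, and it cannot be computed for a patient who starts at 0, that is, with no appetite problem. Under the missing-data rule such patients could drop out of that comparison.

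**Working it through.** **Inputs from the article:** 30 per group, target difference 1 point, SD 1.35, 5% level, two-sample t-test, 64 enrolled for 60 evaluable at 5% attrition.

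**Assumed:** the correlation r between pre-operative and 3-month Q8. The documents give no value, so a range is shown.

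**1. The plan's own figure.** Two-sided t-test (noncentral t), standardised difference 1/1.35, 30 per group: power 80.5%, and 29.6 (so 30) per group needed for 80%. A one-sided 5% test would give 88.3%, so the stated figure is two-sided. Enrolment: 60/0.95 = 63.2, so 64. Both stated figures reproduce.

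**2. Unweighted gain from baseline adjustment.** Residual SD = 1.35 × √(1 − r²), put through the same power calculation:

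| r (assumed) | variance saved (r²) | residual SD | power |
|---|---|---|---|
| 0 | 0% | 1.35 | 80.5% |
| 0.2 | 4% | 1.32 | 82% |
| 0.3 | 9% | 1.29 | 84% |
| 0.5 | 25% | 1.17 | 90% |

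**3. Bias if baseline is left out of both models.** With equal SDs, a baseline difference d that remains after weighting shifts the 3-month contrast by r × d. For d = 0.5 points (assumed): 0.2 × 0.5 = 0.10, 0.3 × 0.5 = 0.15, 0.5 × 0.5 = 0.25 points, against a target of 1 point.

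**4. Weighted analysis, by simulation.** Assumed set-up: n = 60, four other covariates plus baseline Q8, SD 1.35, true difference 1, baseline related to procedure at log-odds 0.4 per SD, robust (HC3) standard errors, 4,000 trials per setting.

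| r | bias, baseline in neither model | bias, baseline in propensity model only | power, propensity model only | power, propensity and outcome models |
|---|---|---|---|---|
| 0.2 | 0.10 | 0.00 to 0.01 | 68% | 68% |
| 0.3 | 0.15 | 0.00 to 0.01 | 68% | 69% |
| 0.5 | 0.25 | 0.00 to 0.01 | 70% | 78% |

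At r = 0.5 the true sampling SD of the estimate barely changes (0.369 to 0.356). Most of that power gain arises because the robust standard error, which treats the weights as fixed, becomes less conservative. In a separate simulation at r = 0.5 with baseline left out of the propensity model, adding it to the outcome model alone brought the bias from 0.26 to 0.00. So the outcome-model term protects the estimate even when the propensity model omits baseline.

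**The case against.** A reader might infer that the plan ignores the baseline score and leaves baseline imbalance in the result. The documents do not support either statement.

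- Baseline is used: percent change is compared, and every MDASI-GI + score is reported before surgery.
- The propensity covariates are unlisted. Pre-operative Q8 is measured and may be among them. A journal article commonly leaves that list to the full protocol or SAP, so its absence here is not an error. If Q8 is included, the simulated bias is essentially zero.
- The precision gain rests on an assumed r. The item has 24-hour recall and is answered up to 30 days before major surgery and again at 3 months, so a low correlation is plausible. At r of 0.2 to 0.3 the weighted gain nearly vanishes once baseline is in the propensity model.
- A weighted difference in 3-month scores is a valid analysis of the stated endpoint.
- Imputing missing baseline scores would conflict with the plan's own missing-data rule.

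All of this stands, and it limits the point to what the article commits to. It does not remove it. The article does state the primary estimator and how baseline enters for this endpoint. The use that it names is a weak one, and a better one needs no new data.

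**Conclusion.** The point holds as a nearly free improvement in precision and in protection against confounding; it does not correct a wrong figure. The stated primary analysis has no baseline term in the outcome model and no commitment to baseline Q8 in the propensity model. Percent change cannot substitute for either.

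The size is conditional. Unweighted power would rise by about 2 to 10 percentage points for r from 0.2 to 0.5. In the weighted analysis, with baseline already in the propensity model, the gain is 0 to 1 point at r of 0.2 to 0.3 and about 8 points at r = 0.5. Bias is roughly 0.1 to 0.25 points only if baseline is related to the choice of procedure and absent from the propensity model; otherwise it largely disappears. The correlations, the strength of the link to procedure and the number of covariates are all assumptions. The sample size and the 80% power for the unweighted t-test are correct as stated.

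**What to change.** - Make the primary analysis a weighted linear regression of 3-month Q8 on procedure and pre-operative Q8, with a robust standard error.
- Name pre-operative Q8 as a covariate in the propensity model.
- Report the adjusted mean difference with its 95% confidence interval as the primary result.
- Replace percent change with this adjusted difference, or label percent change as descriptive.
- State what happens to patients without a pre-operative score: either they are excluded under the existing no-imputation rule, or an explicit exception to that rule is written.

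The cost is a few sentences and no new data. The downside is the possible loss of the few patients who have no baseline score.

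### The supplementary comparison of percent change in appetite is undefined for patients whose baseline score is 0 and depends strongly on baseline for the rest

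*Protocol article*

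**What the plan says.** All the relevant text is in the protocol article.

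- **Direction of the score** (Statistical methods): "The primary outcome is appetite level score (with 0 being the best and 10 being the worst".
- **Meaning of zero** (Additional clinical data): patients rate each symptom "on a scale of 0 (not present) to 10 (as bad as you can imagine". Zero is therefore what a patient without an appetite problem reports.
- **Baseline** (Preoperative evaluation): "Within 30 days prior to surgery, PRO collection will be completed using the MDASI-GI" questionnaire, so each patient should have a baseline appetite score.
- **Primary analysis** (Statistical methods): "For the primary analyses, we will apply the inverse probability treatment weights using propensity scores". Percent change is not mentioned there.
- **Supplementary tests** (Statistical methods): a t-test or rank-sum test is added to the weighted analysis. It covers the month-3 values of both appetite and ghrelin, and the same sentence extends it to a further measure: "as well as the percent change from baseline, between the two cohorts".
- **Missing data** (Statistical methods): "Missing data will be excluded from analysis and no missing data imputation will be performed".

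The article gives no rule for a baseline score of 0.

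**The concern.** Percent change divides by the baseline value. That suits a quantity that is always positive, such as a hormone concentration. It does not suit a symptom score whose best and attainable value is zero. The sentence names appetite and ghrelin together and attaches percent change to both.

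Two things follow. Patients with no appetite problem before surgery have no defined value. They matter to a study whose hypothesis is that proximal gastrectomy preserves appetite, because a loss of appetite is plainly visible in them. For everyone else, the same movement in points counts for more the better the baseline was, so a mean percent change would be pulled by the few patients who start at 1 or 2.

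If the measure stays, someone will have to choose a workaround once the data are in, such as dropping the zeros or adding a constant. That choice is better made now.

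**Working it through.** **The plan's own figures first.** Inputs from Statistical methods: 30 per cohort, a 1-point difference, SD 1.35, 5% level. Whether the test is one- or two-sided is not stated; I take two-sided.

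- Noncentrality = 1 / (1.35 × √(2/30)) = 1 / 0.3486 = 2.87, with 58 degrees of freedom. The two-sided t-test has power 80.5%, which reproduces the stated 80%.
- Enrolment: 60 / 0.95 = 63.2, rounded up to 64, as stated.

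Both figures concern the absolute 3-month score. Neither uses percent change.

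**The measure.** Percent change = 100 × (follow-up − baseline) / baseline. For a fixed worsening on the 0–10 scale:

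| Baseline | Follow-up | Change in points | Percent change |
|---|---|---|---|
| 0 | 3 | +3 | undefined (3/0) |
| 1 | 4 | +3 | +300% |
| 2 | 5 | +3 | +150% |
| 5 | 8 | +3 | +60% |
| 1 | 3 | +2 | +200% |
| 7 | 9 | +2 | +29% (2/7 = 28.6%) |

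The same 2-point worsening counts 200 / 28.6 = 7 times as much at baseline 1 as at baseline 7. The measure is also asymmetric: improvement cannot go below −100%, while worsening from 1 to 10 is 100 × 9/1 = +900%.

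**Does the Wilcoxon option help?** It limits the pull of extreme values on a mean. It does not define a value for baseline 0, and the order it ranks is already distorted: 1 to 3 (+200%) ranks as worse than 5 to 9 (100 × 4/5 = +80%), although the second patient lost twice as many points.

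**How likely is a zero baseline?** The documents give no baseline distribution, so the share p is an assumption. The chance that none of 60 patients scores 0 is (1 − p)^60:

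- p = 5%: 0.95^60 = 4.6%
- p = 10%: 0.90^60 = 0.18%

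Even a small share makes at least one undefined value very likely.

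**How many would remain?** If patients with baseline 0 are left out, 60 × (1 − p) remain in the percent-change comparison:

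| Assumed share with baseline 0 | Remaining of 60 |
|---|---|
| 10% | 54 |
| 20% | 48 |
| 30% | 42 |
| 50% | 30 |

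**On the absolute scale** every patient with both scores has a value, and equal movements count equally: 0 to 3, 1 to 4, 2 to 5 and 5 to 8 are each +3 points.

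**The case against.** **It is not the primary analysis.** This stands. The primary comparison is the weighted one on the absolute 3-month score, the t-test or Wilcoxon test comes in addition, and percent change is a further addition within that. A reader might infer that the main result or the sample size is at risk, or that only 48, 42 or 30 patients would be analysed in the study. The documents do not support that. A baseline of 0 does not remove a patient from the 3-month comparison, and the power calculation never used percent change.

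**The exclusion is inferred.** This stands in part. A patient with both scores observed has no missing data in the strict sense; only the derived ratio is undefined, and a full protocol or analysis plan might say how to treat it. Dropping such patients is the probable reading, because the article offers no other handling, but it is not stated. The defect does not depend on it: the named measure has no value for these patients under any convention that leaves it unchanged.

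**Differential loss is not shown.** This stands. Because procedure follows patient and surgeon preference, baseline appetite could differ between cohorts, and a reader might infer a biased comparison. No section reports baseline appetite by procedure, so this is a possibility only.

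**Percent change may be meant for ghrelin alone.** The grammar allows this but does not favour it, since appetite and ghrelin are named together. If it is meant, the sentence should say so.

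**A mixed model already covers change over time.** The article does plan a linear mixed model for quality of life over time, so percent change is not its only treatment of change. That model is described with time and procedure but no procedure-by-time term, so it does not clearly replace a comparison of change between cohorts. It does not repair the percent-change test either.

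**The article is a condensed text.** The point is not that a detail is left out. The article names a specific measure, and that measure fails for part of the scale.

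**Conclusion.** The point holds for the supplementary comparison only. As written, percent change in the appetite score is undefined at a baseline of 0, and elsewhere equal point changes differ by a factor of up to 7 in the example above. Neither permitted test cures this. These statements follow from the definition of the score alone.

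The number of patients affected rests on two assumptions: the share with baseline 0, which the documents do not give, and the handling of undefined values as missing. At assumed shares of 20%, 30% or 50%, the supplementary comparison would keep 48, 42 or 30 of 60 patients.

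The primary weighted analysis, the 60 evaluable patients and the 80% power are untouched, and no revised sample size is called for. This is a should-fix matter, not one on which the main conclusion depends. Nor do the documents support extending it to the other questionnaire items, body weight or ghrelin: percent change is named only for appetite and ghrelin, and for a positive concentration it is well defined.

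**What to change.** In the supplementary-test sentence of Statistical methods, separate the two variables.

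- **Appetite:** replace percent change with absolute change from baseline in points. The preferable form is a linear model of the 3-month score on procedure and baseline score, using the inverse probability weights already planned. A plain two-sample comparison of absolute change would also remove the defect.
- **Ghrelin:** percent change may stay.

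The cost is one sentence. The baseline and 3-month scores are already collected, so no new data, visits or patients are needed. The change should be made before outcome data are examined.
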